### Outcome measures

Outcome measures used in this study are captured using different data collection tools and are summarised in Table 4. It is anticipated that improvements of blood pressure, lipid levels and glycaemic control will be observable after at least one year as changes have been detected after 12.5 months of implementation in similar evaluation studies (Norris *et al*., 2001). Hence, for post-intervention, information on processes of care (investigations, counselling and prescribing patterns) will be gathered via RCRs 15 months after implementation.

**Table 4. tbl4:** Outcome measures of the EnPHC-EVA: facility study

Outcomes	Indicators		Data Source
	T2DM	Hypertension	
Process of care	Proportion of Patients whose BP and glucose were measured at every visit Patients with HbA1c tests done at least once over the past three months Patients with weight and BMI assessed at least once over the past six months Patients with the following examinations done at least once a year: lipid profile tests, serum creatinine, blood urea nitrogen and urine albumin tests, eye examination (visual acuity and fundus), foot examination and liver function test Patients with cardiovascular risk assessment done within the past one year Patients who received counselling: exercise, dietary Patients who received pharmacotherapy: lipid lowering drugs, insulin and antihypertensives	Proportion of Patients with BP measured at every visit Patients with fasting blood glucose, serum creatinine, urine albumin and lipid profile measured at least once a year Patients with electrocardiogram and cardiovascular risk assessment done within the past one year Patients who received counselling: exercise, dietary Patients who received pharmacotherapy: antihypertensives	RCR
Intermediate clinical outcomes	Proportion of Patients with HbA1c ≤ 7% Patients with BP ≤ 135/75 mmHg Patients with LDL-C ≤ 2.6 mmol/L Patients with HDL-C > 1.0 mmol/L (male) or HDL-C > 1.2 mmol/L (female)	Proportion of Patients with BP < 140/90 mmHg Patients with LDL-C ≤ 2.6 mmol/L Patients with HDL-C > 1.0 mmol/L (male) or HDL-C > 1.2 mmol/L (female)	RCR
Patient disease awareness	Proportion of patients who know their diagnosis		Patient exit survey
Patient experience	Mean score in assessment of care for chronic illness (activation, decision support, goal setting) Proportion of patients who perceived effective patient–provider communication Proportion of patients whose waiting and consultation time matched their expectation		Patient exit survey
Patient satisfaction	Proportion of patients who are willing to recommend the clinic to friends and family		Patient exit survey
Providers’ satisfaction	Mean score on six components of job satisfaction among providers (stress, administrative work, interest, balance between effort and reward, respect and whether their job makes sense to them)		Provider Survey
Providers’ quality of care	Proportion of providers providing quality care and continuous care		Provider survey

BP: Blood pressure; HbA1c: Haemoglobin A1c; BMI: Body mass index; LDL-C: Low-density Lipoprotein Cholesterol; HDL-C: High-density Lipoprotein Cholesterol; TG: Triglyceride.

Improved self-efficacy, improved health beliefs and a clear care pathway are expected to increase patients’ satisfaction with the healthcare system and improve utilisation (Panagioti *et al*., 2014). These outcomes will be captured via a patient exit survey. In addition, this study also includes a measure of potential unintended outcomes, such as the job satisfaction of the healthcare providers involved in implementing the interventions. Patient exit survey and provider survey will be carried out at 20 months post-intervention. In the long run, there are expected to be reductions in complications of T2DM, hypertension and hypercholesterolaemia and improvement in patients’ quality of life. However, this evaluation study was not designed to measure the changes in hypercholesterolaemia and the long-term outcomes.

### Data collection tools and sources

This study gathers data from patient medical records, a self-administered questionnaire for healthcare providers and patient interviews. The data collection tools include a data extraction form for RCR, three questionnaires (patient exit, provider and facility questionnaires) and an intervention checklist. All data collection tools are available in Appendices A–E. All the data collection tools underwent a pre-test for comprehensibility.

#### Data extraction form for retrospective chart review

An electronic data extraction form was designed to collect information on the process of care and intermediate clinical outcomes, as described in Table 4. The source of data extraction is T2DM and hypertension patients’ medical records that were available as paper-based documents, within the legacy tele-primary care (TPC) computer system or any standalone electronic medical system.

#### Patient exit questionnaire

The research committee comprising intervention implementers, family medicine specialists (FMS), public health specialists and study researchers had reached a consensus to adapt a subset of items from the Quality and Cost of Primary Care (QUALICO-PC): Patient Experience Survey (Sivasampu *et al*., 2016) and the Patient Assessment of Chronic Illness Care (PACIC) survey instruments (Glasgow *et al*., 2005) for the patient exit questionnaire. This decision was reached after taking into account the length of the questionnaire and health literacy level of the study population (Azreena *et al*., 2016) in order to reduce respondent fatigue and increase completion rates. The questionnaire contained 43 items and was completed through face-to-face interviews, which measure socio-demographic characteristics, patient experience and satisfaction, disease awareness and self-management support.

#### Provider questionnaire

Similarly, the research committee adapted the questions from QUALICO-PC: General Practitioner questionnaire (Sivasampu *et al*., 2016) for the provider questionnaire. The main aim of the provider survey is to gather information on job satisfaction. The decision to measure job satisfaction is based on the conceptual framework that was described in the earlier section. Six components of job satisfaction are measured, which include stress, administrative work, interest, balance between effort and reward, respect and whether their job makes sense to them. It also measures the use of latest clinical practice guidelines, continuity and coordination of care and workload. As such, a self-administered provider questionnaire consisting of 28 questions, which focused on the structural aspects of primary care, workload, demographic and the provider’s satisfaction, was developed.

#### Facility questionnaire

The facility questionnaire was developed to measure information on clinic resources, including staff, infrastructure and equipment, as well as services provided, which can determine the success of the intervention.

#### Translation of English version questionnaires into Malay language

The translation of the English version of the patient exit questionnaire, provider questionnaire and facility questionnaire into Malay language was performed using forward and backward procedures. Two study collaborators who were fluent in both English and Malay and familiar with the primary care practice prepared the Malay questionnaire. The Malay questionnaire was then back-translated into the English version independently by another two translators. The researchers compared both versions to ensure that no change in the context occurred during translation and discrepancies were resolved prior to pre-test of the surveys. Subsequently, modifications of the Malay version questionnaire were made in accordance to findings of the pre-test.

#### Intervention checklist

As the EnPHC framework is a complex intervention with multiple elements, it is important to measure the details of its implementation at each clinic in order to quantify the percentage of the intended interventions that actually took place, the level of contamination within control clinics and also to determine the correlation between the degree of implementation and the observed outcomes (O’Donnell, 2008). This is important as contamination is expected as some of the EnPHC intervention components are built upon existing primary care programmes (Safurah *et al*., 2018) (Refer to Table 1).

The 18-item intervention checklist was checked for content validity through a consensus meeting with ten content experts who were EnPHC intervention implementers. The implementers weighed the items based on the expected impact of each item on the study outcomes. The final score of the intervention checklist will be reported as a percentage and used as a covariate in the analysis.

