The conceptual framework to guide the implementation and evaluation is discussed below. An impact evaluation that spans from the community to the patients and providers of primary healthcare is carried out (Institute for Public Health, 2019a). To further strengthen the findings from the impact evaluation studies, a process evaluation study is carried out to evaluate the implementation process in terms of fidelity and quality of implementation (Institute for Health Systems Research, 2019).

To evaluate the interventions, complementary data from multiple sources are used to measure outcomes. Evaluation performed at primary healthcare clinics aims to measure health service and patient outcomes. Therefore, the primary objective is to evaluate the impact of EnPHC interventions on processes of care and intermediate clinical outcomes among T2DM and hypertension patients, and the secondary objective is to evaluate the impact of the EnPHC interventions on patients’ experience and providers’ job satisfaction. The aim of this paper is to describe the sequential steps taken to evaluate the EnPHC interventions at primary healthcare clinics (EnPHC-EVA: Facility) and the methods used.

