#### Difference-in-differences

DiD analysis will be used to analyse all outcome measures. DiD analysis measures the average effect of the interventions, taking into account two differences: first is the difference between the intervention and control arm and second is the difference between pre- and post-intervention (Gertler *et al*., 2011; Dimick *et al*., 2014). As this is a large-scale field experiment, the difference at baseline is often not negligible and must be accounted for when measuring the intervention effect.

A multivariable model that controls for patient- and clinic-level covariates will be used. Details on the key covariates for each objective can be found in Appendix F. For RCR, patient visits from November 2016 to June 2017 will be grouped to estimate outcome levels in the pre-intervention phase and those from October 2018 until June 2019 will be grouped to estimate outcomes after 15 months of intervention.

Generalised estimating equations will be used to estimate the parameters for both linear and non-linear outcomes while adjusting for clustering at the clinic level. Thus, cluster robust standard errors will be reported. In addition, the key assumptions for DiD analysis which are ‘common shocks’ and ‘parallel trends’ will be checked where trend data are available.

The ‘geeglm’ function from the ‘geepack’ package in *R* will be used to perform the analysis (Yan, 2002; Yan and Fine, 2004; Højsgaard *et al*., 2005). For RCR outcome measures that will be reported as proportions, the DiD estimates will be reported as odds ratios with 95% confidence intervals. For provider survey and patient exit survey outcome measures, the DiD estimates will be reported as changes in means with 95% confidence intervals.

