#### Interrupted time series

ITS analysis will examine changes in trends and levels of the outcome measures using monthly data. The observation period started in November 2016 while the interventions were implemented from July 2017. Data from August 2017 to September 2018 will be used to plot a segment to show trend or level change during intervention whereas data from October 2018 to June 2019 will be used to measure the change after 15 months of intervention. ITS analysis can provide an insight into the expected trends of changes, especially for measures that do not show immediate effects. This can show the potential benefits of the interventions, even though the differences in levels are not significant in the early stage of the intervention.

Equivalence of baseline trends in intervention and control groups will be checked. If equivalence cannot be ensured, we will not infer causality between intervention and outcome (Lopez Bernal *et al*., 2018). We assume an impact model with both level and trend change for all outcomes. The final model will be estimated using generalised least squares. All covariates are included based on clinical relevance, hence this will be retained in the model regardless of statistical significance. The ‘nlme’ package in *R* will be used for segmented regression (Pinheiro *et al*., 2013). Results will be presented in ITS charts with the corresponding statistical results for trend and level changes post-intervention.

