Hypercholesterolaemia was among the NCDs that were shown to be under-diagnosed and suboptimally managed in Phase 1 of the Malaysian Health Systems Research (MHSR) report (Ministry of Health Malaysia and Harvard University TH Chan School of Public Health, 2016). EnPHC-EVA: Facility study was designed to include a sub-sample of hypercholesterolaemia patients but this plan had to be dropped because there was no means to identify a list of patients diagnosed with hypercholesterolaemia. Patient visits for T2DM and hypertension, on the other hand, had defined appointment registers for each clinic work day. However, T2DM and hypertension patients with hypercholesterolaemia as comorbidity were captured.

Process evaluation of EnPHC interventions in the primary healthcare clinic is conducted by a separate study team to improve execution of the interventions. This, together with an impact evaluation done at both the community and facility level, will complement each other and allow for triangulation of findings. Only then, the intervention can be refined and replicated for further nationwide scale up.

The strengths of this study include the presence of a control group, random intervention allocation and repeated data points which maintained internal validity. Furthermore, the clusters were matched to minimise bias that can exist from differences in clinic composition. An intervention checklist was also incorporated to adjust for the degree of intervention implementation within each clinic and explain potential contamination or incomplete implementation in the control and intervention clinics, respectively. In addition, the transparency in reporting this study by adhering to the Transparent Reporting of Evaluations with Nonrandomized Designs (TREND) statement is a form of knowledge sharing and contributes to rigorous evidence to guide future research and practice (Des Jarlais *et al*., 2004). Another strength of this study is that its implementation and evaluation teams were from separate institutions, the former is a planning and governing division for public health clinics while the latter is a research organisation. This maintained objectivity of the study and minimises the risk of publication and outcome-reporting bias. Lastly, this study also captures potential unintended effects on the healthcare staff, measured as change in health provider job satisfaction following the implementation of EnPHC through the provider survey.

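### The plan adjusts for the checklist score of delivered intervention; depending on its coding, this biases the difference-in-differences effect towards zero or adjusts for nothing

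*Protocol article*

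**What the plan says.** Under Intervention checklist, the protocol article describes an 18-item instrument meant, among other things, to "quantify the percentage of the intended interventions that actually took place, the level of contamination within control clinics". It is therefore scored in both arms and records what happened after allocation. On the weights it says: "The implementers weighed the items based on the expected impact of each item on the study outcomes". On its use: "The final score of the intervention checklist will be reported as a percentage and used as a covariate in the analysis".

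The Discussion lists this among the strengths: "An intervention checklist was also incorporated to adjust for the degree of intervention implementation within each clinic". The same sentence says the checklist will help explain contamination in control clinics and incomplete implementation in intervention clinics.

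The Introduction gives the target of estimation: "the primary objective is to evaluate the impact of EnPHC interventions on processes of care and intermediate clinical outcomes among T2DM and hypertension patients". Under Difference-in-differences, the effect model is described thus: "A multivariable model that controls for patient- and clinic-level covariates will be used". The covariates themselves are left to Appendix F, which is not shown. The article describes two effect models, the DiD and the interrupted time series (ITS). It describes no version of either without the checklist score, and no separate analysis to which the score is confined.

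**The concern.** The score is a consequence of allocation and is built to track the route by which the package acts, since its items are weighted by the outcome impact expected of them. A model that holds it constant asks what allocation does when clinics deliver the same amount of the package. That is not the overall impact named as the primary objective. If the package works through its components, as the article's theory of change supposes, the adjusted quantity shrinks towards zero however well the package works.

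The project is meant to inform a decision on national expansion. An effect biased towards zero could count against a package that works. If instead the score enters in a form that leaves the estimate alone, readers are told that contamination and incomplete delivery have been adjusted for when they have not.

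**Working it through.** **1. Effect size used.** The article gives no figure for this point, so the T2DM sample size supplies the effect. 52.5% × 1.28 = 67.2%, a difference of 14.7 percentage points; odds ratio (0.672/0.328)/(0.525/0.475) = 1.85. The stated 900 visits per arm reproduces from the stated inputs. With 45 visits in each of 20 clinics and ICC 0.091, the design effect is 1 + 44 × 0.091 = 5.004. The standard error is √[(0.525 × 0.475 + 0.672 × 0.328) × 5.004/900] = 0.0511, and 0.147/0.0511 = 2.88. This gives 80% power on a t distribution with 38 degrees of freedom.

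**2. What each coding does, in a linear model.** Let θ be the true DiD effect, f the share of θ that runs through the score, and r the within-arm reliability of the recorded score.

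- *One fixed value per clinic, main effect only.* The value is the same before and after, so it cancels from each clinic's change. The arm-by-period term is unchanged; only the arm main effect moves.
- *Period-specific value.* The model attributes about f × r × θ to the score, so about θ(1 − f × r) is left for the arm-by-period term.
- *Post-period value with a score-by-period term.* Each clinic's change is regressed on arm and score, so part of θ passes to the score term.

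**3. Clinic-level linear simulation.** 20 v 20 clinics, 800 runs per setting, cluster-robust standard errors, clinic SD 0.15 (√(0.091 × 0.525 × 0.475) = 0.151). The whole effect acts through an error-free score. Mean scores (control/intervention) are assumed, because the article gives none. Entries are the mean DiD estimate and, in brackets, the proportion of runs significant at 0.05.

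| Coding of the score | 30/80% | 50/70% | 10/95% |
|---|---|---|---|
| Not in model | 0.146 (0.99) | 0.147 (0.95) | 0.139 (0.99) |
| Fixed value, main effect only | 0.146 (0.99) | 0.147 (0.95) | 0.139 (0.99) |
| Post-period value with score-by-post term | 0.068 (0.15) | 0.065 (0.25) | 0.067 (0.09) |
| Period-specific value | −0.002 (0.08) | 0.001 (0.06) | −0.015 (0.09) |

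In the last column, limiting scores to 0–100% lowers the true effect slightly. With the score-by-post term the loss is 1 − 0.068/0.146 = 53%, 1 − 0.065/0.147 = 56% and 1 − 0.067/0.139 = 52%. That fraction reflects how scores were generated: control scores carried over with a drift SD of 0.05, and intervention scores were redrawn with SD 0.10. The pooled within-arm slope of score change on post-period score is then (0.05² + 0.10²)/(0.10² + 0.05² + 0.10²) = 0.0125/0.0225 = 0.56, which matches.

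**4. Visit-level logistic simulation.** 40 clinics, 80 pre and 90 post visits per clinic (ten per month over 8 and 9 months), ICC 0.091, odds ratio 1.85 acting wholly through the score, 1,000 runs. Assumed scores: 30% at baseline, then 80% in intervention and 40% in control clinics, SD 10.

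- Without the score: mean log odds ratio 0.563, power 93.8%.
- Fixed value: 0.572, power 94.6%.
- Period-specific value: 0.011, power 7.5%; the SD of the estimate rises from 0.16 to 0.32.

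**5. Relaxing full, error-free mediation.** Linear DiD, same assumed scores as in step 4, period-specific coding, 1,500 runs per setting, compared with 1 − f × r:

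| f | r | Effect remaining, simulated | 1 − f × r |
|---|---|---|---|
| 1 | 0.7 | 31% | 30% |
| 1 | 0.5 | 50% | 50% |
| 0.7 | 0.7 | 52% | 51% |
| 0.5 | 0.5 | 75% | 75% |

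No ITS model was simulated, so no size is given for that analysis.

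**The case against.** The strongest reply is that the article speaks of one final score and describes no baseline checklist and no checklist per phase or month. The plain reading may be a single value per clinic, and on that reading both simulations show no harm to the DiD estimate. Moreover, neither analysis section names the checklist, Appendix F is not shown, and the checklist section also mentions correlating implementation with outcomes, for which using the score as a covariate would be proper.

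Much of this stands. The coding is unknown, and the size of any bias is conditional on it. But the word *final* may mean only the weighted total. The covariate sentence is not limited to the correlation analysis, and the Discussion says the purpose is to adjust. The single-value reading does not rescue the text either, because the adjustment claimed as a strength then does nothing to the estimate.

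Four stronger inferences are tempting and are not supported:

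- *Power will collapse from 94% to 7.5%.* This needs a period-specific score and full, error-free mediation. The article states neither, and reports only content validity for the checklist.
- *The randomised comparison is lost.* This follows only under codings that alter the arm-by-period term.
- *The score is nearly collinear with arm.* No score levels are given, contamination is expected, and several components already exist in part under the current model, so the arms may overlap.
- *The ITS is damaged in the same way.* The statement "All covariates are included based on clinical relevance, hence this will be retained in the model regardless of statistical significance" does not name the checklist, and nothing shows that a monthly score exists.

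**Conclusion.** The concern holds in conditional form. The plan states that it will adjust for a post-allocation measure on the causal path, and this does not fit its objective of overall impact.

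- If the score varies by period or interacts with period, the DiD effect is biased towards zero. About half is lost with a score-by-post term. Nearly all is lost with a period-specific score under full, error-free mediation, and between 25% and 69% in the four less extreme settings examined.
- If the score is one fixed value entered as a main effect, the estimate is essentially unchanged, and the claimed adjustment for incomplete implementation and contamination does not occur.

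All sizes rest on assumed score levels and on the simulated link between pre- and post-period scores. The direction does not depend on the particular score levels chosen. The point should be fixed, but it is not shown to defeat the primary analysis. Confidence is medium, because neither the coding nor Appendix F is available.

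**What to change.** Estimate the main DiD effects by allocated arm without the checklist score, and apply the same rule to the ITS. Use the score only in a separately labelled secondary analysis of dose-response or fidelity, stating there how it is coded and when it is measured. Reword the covariate sentence under Intervention checklist and the strengths sentence in the Discussion to match, and remove the score from the main-model covariates in Appendix F if it is listed there.

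An instrumental-variable analysis, with allocation as the instrument for the score, is optional. It would have to assume that allocation affects outcomes only through what the score measures.

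The cost is two sentences and possibly one entry in the covariate list. No new data are needed and the sample size does not change.
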